## Abstract

**Background:**

Behavior change interventions have been the focus of recent studies, and the COVID-19 pandemic highlighted the importance of online interventions. However, no previous studies have investigated behavior change techniques to improve physical activity in adults with asthma through online intervention.

**Methods:**

This double-blind clinical trial will investigate the effectiveness of an online behavior change intervention in increasing physical activity and reducing sedentary behavior in adults with asthma, as well as in improving other clinical outcomes in short and medium terms. Patients with clinically stable moderate to severe asthma, who are physically inactive and do not have cardiovascular and/or osteoneuromuscular impairments will be randomized into control or intervention groups (23 in each). Both groups will carry out an online educational program (1 h). Additionally, the intervention group will receive weekly individual online sessions for 12 weeks of motivation-based behavior change intervention to promote an increase in physical activity and reduce sedentary behavior based on both self-determination theory and transtheoretical model. The intervention group will also receive an activity monitor with specific strategies related to it. Both groups will be reassessed immediately after the intervention and 6 months after that. The primary outcomes are physical activity and sedentary behavior, which will be objectively assessed by a triaxial accelerometer (Actigraph wGT3X-BT). Secondary outcomes are Asthma Control Questionnaire, Incremental Step Test, Sit-To-Stand, Timed Up-and-Go, 4-Metre Gait Speed, Asthma Quality of Life Questionnaire, Pittsburgh Sleep Quality Index, Epworth Sleepiness Scale, Actiwatch 2, and the Hospital Anxiety and Depression Scale.

**Discussion:**

The intervention is unprecedented and was carefully developed to joint most characteristics and techniques of both behavioral strategies (transtheoretical model and self-determination theory). Therefore, this intervention has the potential to improve physical activity levels and asthma management and reduce sedentary behavior. As a consequence, this novel intervention will improve global health in this population and support its use in clinical practice. The intervention will be carried out online with direct weekly contact with the therapist. Consequently, it has low implementation costs, might improve patient’s attendance, and has the potential to be largely offered elsewhere.

**Trial registration:**

ClinicalTrials.govNCT05241223. Registered on January 22, 2022.

## Background

Behavior change (BC) interventions have been used to promote physical activity (PA), including PA level increment [1]. Several BC models have been tested such as the self-determination theory (SDT). The SDT aims to facilitate BC by supporting individuals’ basic psychological needs (BPN) (i.e., autonomy, competence, and relatedness) and, consequently, fostering volitional and high-quality forms of motivation for behavioral engagement, including PA improvement or maintenance [2].

Evidence suggests that BC strategies focused on BPN are due to increase more internal forms of motivation and facilitate PA performance, PA maintenance, and positive changes in health outcomes [2, 3]. Relatedly, the transtheoretical model (TTM) observes that BC happens by stages (of change) and each stage represents the individuals’ motivational disposition to adopt/maintain or not a behavior. The TTM considers that BC involves a set of changing processes that people experience to progress through these stages, along with decisional balance, self-efficacy, and temptations [4].

Individuals with chronic diseases are more likely to engage in low physical activity levels [5]. In addition to the disease burden, low PA levels may result in even detrimental consequences, including high mortality risk [6]. In contrast, PA improves multiple health benefits, and recent literature has shown the importance of people’s pleasure and enjoyment in becoming more physically active [7]. Therefore, interventions using BC strategies are particularly important in this population [7].

Studies have suggested that regular PA is associated with a reduction of depression symptoms and systemic inflammation, as well as improvement in exercise capacity, asthma control, and sleep quality in adults with asthma [8, 9]. However, this population still performs less PA than people without asthma [10]. Few studies aiming at improving PA in adults with asthma through BC techniques have been developed [11–14]. They were effective in increasing PA; however, it remains unclear whether these results are maintained over time and whether an online intervention is also effective in people with asthma. Furthermore, none of these studies used the well-established SDT to facilitate BC.

## Methods

### Aims

The primary aim of this randomized clinical trial is to investigate the effectiveness of an online BC intervention based on both SDT and TTM in increasing PA and reducing sedentary behavior in adults with asthma. Secondary aims are (I) to observe the impact of this intervention on asthma control, functional capacity, quality of life, sleep quality, and symptoms of anxiety and depression; (II) to verify whether the BC intervention improves the satisfaction of BPNs, self-determination and autonomous forms of motivation for PA; and (III) to investigate if the effects of the BC intervention will be maintained in the medium term (6 months after the end of intervention).

### Design and setting

This double-blind (trial participants and outcome assessors) multicenter randomized clinical trial is expected to be carried out between February 2022 and November 2023. Patients will be contacted by a researcher involved in this study, informed about the study, and invited to participate. If they agree to participate, the inclusion criteria will be applied. All patients will be assessed before and immediately after the intervention (i.e., after the 12 weeks of intervention commencement), as well as 6 months after that (Fig. 1). Patients who discontinue the intervention protocol will be invited to a follow-up assessment. Research assessments will be carried out in person by trained assessors in both centers (Londrina and São Paulo), and the interventions will be carried out online by the main investigator from the coordinating center (Londrina).

**Fig. 1 Fig1:**
[figure not shown]
SPIRIT schedule of study enrolment, interventions, and assessments (*−t1=* enrolment; *0*= allocation; *t*_*1*_= post intervention; *t*_*2*_= 6 months after the end of intervention)

After the initial assessment, patients will be randomized into 2 groups: control group (CG) or intervention group (IG). Both groups will receive a minimal intervention (educational program), which will be explained further. The IG will receive weekly individual online sessions and also some online group sessions for 12 weeks of motivation-based BC intervention to promote PA and reduce sedentary behavior. The intervention group will also receive an activity monitor with instructions on how to use. Patients will be instructed to maintain their controller asthma medications during the intervention; however, if it is needed to change, they should record it in the asthma symptoms and medication control diary (explanation further). The study flowchart is shown in Fig. 2.

**Fig. 2 Fig2:**
[figure not shown]
Study flowchart. The assessment will be carried out in one visit. Both groups will carry out a minimum educational program; the intervention group will receive weekly individual online behavior change intervention sessions for 12 weeks and will receive an activity monitor with its specific strategies. Both groups will be reassessed immediately after the intervention as well as 6 months after that

### Participants

Participants will be recruited through the referral of pulmonologists from outpatient clinics of Londrina and São Paulo, Brazil. Study publicization will be performed on social media too; however, patients who come in contact must be undergoing medical follow-up. This study will include people aged from 18 to 60 years, with a physician-based diagnosis of moderate to severe asthma (confirmed by checking the history of variable respiratory symptoms and treatment [15]) who underwent drug treatment for at least 6 months; with clinical stability for at least 1 month (without hospitalizations, emergency care use or medication changes). Additionally, absence of cardiovascular and/or osteoneuromuscular diseases that could interfere/hinder the performance of tests and physical activity, absence of lung diseases other than asthma, preserved cognitive function [16], non-smokers or ex-smokers with <10 pack-years, report being physically inactive in accordance with current physical activity guidelines [17], and people who are able to make video calls through any platform and/or free app available. The exclusion criteria comprise the presence of any physical limitation that compromises mobility and hinders PA performance during the participation period.

### Interventions

#### Educational program

The educational program will be delivered similarly to both groups through videos, images, and a booklet. After the initial assessment, all participants will receive a quick welcome video call, in which they will be randomized (see details further) and informed on how this program will work. After that, the educational videos and booklet will be sent daily for 5 subsequent days. Later, one educational image will be sent every other week up to the 12 weeks completion. Participants will be able to ask questions any time, if they want to. The program will cover information regarding the respiratory system, asthma pathophysiology and treatment, prevention strategies, and medication instructions [15]. It will also be briefly addressed the subjects: understanding PA and sedentarism, as well as the importance and benefits of being physically active and less sedentary [17].

#### Behavior change intervention

The IG group will receive an online intervention based on the TTM [4], along with SDT strategies [2]. A detailed protocol was carefully developed for the study aiming to make the most of the characteristics and techniques of each approach for the proper purposes. The intervention will take place weekly summing up 12 online individual sessions of approximately 30 min each. Four out of the 12 sessions will be carried out in group. The sessions will be made through a platform and/or application that makes video calls privately. Each session will address a topic (Table 1). In addition, in all sessions, the patients’ gain during the previous week will be recognized, as well as new goals will be set for the next week. The goals will always be individualized, realistic and achievable, based on the identification of each person's capacity and motivation [13].

**Table 1 Tab1:** Behavioral change intervention sessions

Week	Theme	TTM	BPN	Main approach
1	Getting to know the patient		Autonomy	Test during the week types of PA which the patient can perform
			Competence	Train in the session PA/exercises that the patient can perform/knowing the activity monitor
			Relatedness	Know previous experiences of the patient related to PA/introduce the group
2	Why to be physically active?	Self-liberation (making a commitment)	Autonomy	Choose the when, how, and the type of PA that will perform
			Competence	Achievable goals, but with a certain challenge (contract)
			Relatedness	Contract is a commitment between the patient the therapist
3	Monitoring (group session) ^a^challenge	Contingency management (Using rewards)	Autonomy	Celebrating small victories
			Competence	Group challenge (gamification)
			Relatedness	Encouraging them to achieve the week group goals
4	Barriers to PA	Stimulus control (Managing the environment)	Autonomy	Recognition of the patient’s perspective on barriers
			Competence	Identifying barriers and indicating ways to overcome them
			Relatedness	Use an object with a color that represents the group
5	Sedentary lifestyle (group session)	Counterconditioning (using substitutes)	Autonomy	Recognizing environmental potential to reduce sedentary lifestyle and increase PA
			Competence	Focus goals on the process
			Relatedness	Encouraging reminders to reduce sedentary lifestyle and increase PA in the group
6	Goals review	Consciousness raising (getting the facts)	Autonomy	Visualizing the progress
			Competence	Controlling of patient evolution/learning calculation of average and goal of steps per day of the week
			Relatedness	Strengthening the bond between patient and therapist
7	Responsibility	Dramatic relief (paying attention to feelings)	Autonomy	Awareness of the importance of attendance
			Competence	Giving positive feedback
			Relatedness	Understanding feelings related to PA
8	Social support ^a^challenge	Helping relationships (getting support)	Autonomy	Discussion on what motivates to continue doing PA
			Competence	Challenge of doing PA with a person this week
			Relatedness	Searching for social support
9	Perceived benefits (group session)	Environmental revaluation and social liberation	Autonomy	Recognition of the patient’s perspective
			Competence	Feedback on how or not you achieved the result
			Relatedness	Exchanging experiences with the group
10	Possible relapses	Temptation	Autonomy	Action plan ideas
			Competence	Drawing up action plans for possible relapses
			Relatedness	Strengthen the group’s bond
11	Self-re-evaluation	Self-revaluation (creating a new self-image) and decisional balance (pros and cons)	Autonomy	Guidance with intrinsic objective
			Competence	Training/teaching things they failed to do
			Relatedness	Strengthen bonds with people close to them
12	Long-term goals (group session)		Autonomy	A leadership profile will be responsible for the group
			Competence	Providing encouragement and support
			Relatedness	Strengthen the group’s bond

The intervention will be delivered once a week for 12 weeks. The program will encompass the processes of change and other TTM techniques. Every session will include the BPN issues (autonomy, competence and relatedness) to facilitate intrinsic motivation from the self-determination theory. *TTM* transtheoretical model, *BPN* basic psychological needs.

^a^Challenges will be used as a form of gamification to move to “another level”

In addition, the IG participants will receive a Fitbit Zip (Fitbit, San Francisco, California, USA) [18] before the first session, which will be used to propose objective goals aimed at increasing PA. Patients will be instructed to wear it on the right side of the waist during the waking period and to remove it only for activities involving water and sleeping. Through the Fitbit Zip display, patients can visualize the number of steps given, as well as estimated energy expenditure and distance covered in the day. Patients will be advised to record these values daily, at the end of the day, in a diary delivered at the beginning of the intervention. This way, patients will be able to know how close they are to the goal and if they reached the goal.

In the weekly sessions, the Fitbit Zip diary data will be revised, and the goal for the next week will be established from the average of the 4 most active days of the previous week [19] with an increase of 6 to 10% steps per week, if the patient feels ready for it (Fig. 3). If the patient does not reach the target in some week but performs an activity that makes him/her happy, he/she will be acknowledged for that. Additionally, a complex practice environment will be created around this device, in accordance with the SDT, such as the visualization of the number of steps evolution and competitions/games with other participants, among others.

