### Sample size calculation

The sample calculation was based on a previous study with adults with asthma in which two groups performed a 12-week intervention to increase physical activity, and the number of steps/day obtained in both groups (control and experimental) were normally distributed with the following values after the intervention: 6248±2030 and 8853±3320 steps/day, respectively [11]. Therefore, for the present study, a total sample of 38 people will be needed to reject the null hypothesis, with a power of 0.8 and a value of *P*<0.05. However, considering a 20% drop-out rate [13] throughout the study, the final sample size will be 46 people (23 in each group).

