### Statistical analysis

Statistical analysis will be performed after post-intervention and follow-up assessments using the software SPSS Statistics V22.0 (IBM, USA). Data distribution will be analyzed using the Shapiro-Wilk test. Variables will be presented as mean (SD), median [interquartile range 25–75%] according to data distribution. Categorical variables will be presented as absolute and relative frequency. The magnitude of statistical estimates will be presented using 95% CI. The results will be analyzed according to the intention-to-treat principle, as recommended by the CONSORT statement [40]. Per-protocol analysis might be performed to contrast results. Mixed model ANOVA will be used to identify the effect of the protocol to promote physical activity and reduce sedentary behavior. The repeated measures factor will be “time” (pre- and post-intervention evaluation) and the independent measures factor will be the “group” (control group or intervention group). To compare the proportion of patients that achieved the minimal clinical important difference in ACQ and AQLQ (0.5 points for both) [22, 41] between groups, the chi-square test will be used. Pearson or Spearman correlation coefficients will be used to verify the relationship between the changes in PA and changes in asthma control or quality of life. Values of *P* <0.05 will be considered statistically significant.

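### The intervention arm meets in shared session groups, but the planned ANOVA and the sample size treat all patients as independent; any differences between session groups would make the interval too narrow

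*Protocol article*

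**What the plan says.** The Randomization and blinding section describes one sealed envelope per patient, so the unit of randomisation is the individual.

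The Behavior change intervention section then says "Four out of the 12 sessions will be carried out in group", and Table 1 marks weeks 3, 5, 9 and 12 as the group sessions. Table 1 introduces the group in week 1. In week 3 it lists a group challenge and "Encouraging them to achieve the week group goals". Later weeks add an object in the group's colour, reminders shared in the group and work on the group's bond. The text on the activity monitor adds "competitions/games with other participants". Controls receive only the educational programme and have no groups. Group size, number of groups and how groups are formed are not stated.

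The Statistical analysis section says "Mixed model ANOVA will be used to identify the effect of the protocol to promote physical activity and reduce sedentary behavior". It names time (pre and post) as the repeated factor and trial arm as the only between-patient factor; the word group there means the arm, not the session group. The Sample size calculation section says "a total sample of 38 people will be needed to reject the null hypothesis, with a power of 0.8", and its only inflation is for drop-out ("considering a 20% drop-out rate").

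**The concern.** Patients who share sessions, a challenge, goals and games may end up more alike in steps and sedentary time than patients from different session groups. This can happen in the intervention arm only, which makes the design partially nested. An ANOVA with time and arm as its only factors has no term for this dependence. It would then understate the standard error of the arm difference for both primary outcomes, and a result just under the 5% threshold could owe something to one unusually active session group. The sample-size section gives 0.8 without saying that it rests on independent patients.

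This is not a detail left to a separate analysis plan: the article itself names the model, its factors and the basis of the sample size.

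**Working it through.** **Inputs from the protocol.** Post-intervention steps/day in control and experimental groups: "6248±2030 and 8853±3320 steps/day, respectively". Significance: "Values of *P* <0.05 will be considered statistically significant", taken as two-sided because the sidedness is not stated. Evaluable patients: 38/2 = 19 per arm.

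**Assumed, because the protocol gives neither.** Session-group size m of 4 to 6; ICC of 0.01, 0.05 or 0.10.

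**Step 1: reproduce the stated sample size.** Difference = 8853 − 6248 = 2605. Pooled SD = √((2030² + 3320²)/2) = 2752. Standardised difference = 2605/2752 = 0.947. The noncentral t gives power 0.788 at 18 per arm and 0.810 at 19, hence 2 × 19 = 38. Then 38 × 1.2 = 45.6, rounded up to 46. The stated figures are recovered with no allowance for grouping.

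**Step 2: standard error with clustering in the intervention arm only.**

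SE = √((2030² + [1 + (m − 1)ICC] × 3320²)/n)

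Since 3320²/(2030² + 3320²) = 11,022,400/15,143,300 = 0.728, the ratio of true to reported SE is √(1 + 0.728(m − 1)ICC), whatever n is. For m = 6 and ICC 0.05 this is √1.182 = 1.087. At 19 per arm the SE goes from 893 to 971 steps/day.

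**Step 3: false-positive rate of the unadjusted test.** 2[1 − Φ(1.96/ratio)]. For m = 6 and ICC 0.05: 1.96/1.087 = 1.80, giving 0.071.

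| ICC | SE excess, m = 4 | SE excess, m = 6 | False-positive rate, m = 4 | False-positive rate, m = 6 |
|---|---|---|---|---|
| 0.01 | 1.1% | 1.8% | 5.3% | 5.4% |
| 0.05 | 5.3% | 8.7% | 6.3% | 7.1% |
| 0.10 | 10.4% | 16.8% | 7.6% | 9.3% |

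A simulation of a t-test on post-intervention steps (40,000 runs per scenario) gave 5.6%, 7.0% and 9.4% for m = 6.

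**Step 4: power at 19 per arm.**
- *Unadjusted test.* At ICC 0.05 the simulated power is about 0.79-0.80, against 0.81 without clustering. The test keeps its too-small standard error, so its rejection threshold does not move.
- *Group-adjusted test* (session-group means, Satterthwaite degrees of freedom). At ICC 0.05 power is about 0.65 with 5 groups and 0.60 with 4. At ICC 0 it is already only about 0.70 and 0.66.
- *Source of the loss.* The share present with no clustering is (0.81 − 0.70)/(0.81 − 0.65) = 0.11/0.16, about 69%, with 5 groups, and (0.81 − 0.66)/(0.81 − 0.60) = 0.15/0.21, about 71%, with 4. Most of it comes from the few degrees of freedom that few groups leave.

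**Step 5: what these figures do not cover.** They concern post-intervention steps, whereas the planned test is the time-by-arm comparison, which depends on the ICC of the change. If session groups form after baseline and the pre and post SDs are equal, that ICC is ICC/(2(1 − r)), where r is the pre-post correlation. The protocol does not give r. A post-intervention ICC of 0.05 becomes 0.05/1.4 = 0.036 at r = 0.3, stays 0.05 at r = 0.5, and becomes 0.05/0.6 = 0.083 at r = 0.7. The inflation for the planned test could therefore be smaller or larger than in the table.

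**The case against.** The best reply is that the protocol does not show that session groups will differ. Eight of the 12 sessions are individual, goals are said always to be individualised, and each weekly step goal comes from the patient's own most active days. Games with other participants could spread members apart as well as pull them together. At ICC 0.01 with small groups the effect is negligible. All of this stands, and it is why the point is conditional.

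A reader might infer that 0.8 power contradicts the purpose of the group sessions. It does not. Sessions that raise steps equally in every group are part of the treatment effect and leave the ICC at zero; only differences between session groups cause clustering.

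A reader might also take the case of one or two very large groups, where the same formulas give much worse error rates (about 14% for one group of 23 at ICC 0.05). Recruitment from February 2022 to February 2023 brings about 23/12, or two, intervention patients a month, so groups of 12 or 23 following the same weekly sequence are unlikely.

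Finally, one could say that naming two factors does not rule out a further sensitivity model in an analysis plan that is not shown. That is true, but the analysis the article fixes has no session-group term, and the membership data must be collected whatever that plan says.

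**Conclusion.** The point holds in conditional form. The design can create dependence among intervention patients, and neither the stated ANOVA nor the stated sample size allows for it. With assumed groups of 4 to 6 and ICC 0.05, the effect on post-intervention steps is modest: one to two percentage points of extra false positives. It is negligible at ICC 0.01 and reaches roughly 2.5 to 4.5 points at ICC 0.10. The size for the time-by-arm test cannot be fixed from the protocol.

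Two stronger readings are not supported. One is that the standard error is too small as a matter of fact: that needs a positive ICC, which the protocol neither states nor implies with certainty. The other is that the trial is underpowered at 0.60-0.65: those figures belong to a group-adjusted test and arise mostly from having few groups. For the same reason, making the adjusted model primary would be a costly trade rather than a plain correction.

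**What to change.** - **Data.** Record the session group of every intervention patient while sessions are running. The therapist already knows it.
- **Statistical analysis section.** Keep the planned analysis as primary. For steps/day and sedentary time, pre-specify as a sensitivity analysis a partially nested mixed model: a random session-group effect in the intervention arm only, a separate residual variance for each arm, and Satterthwaite or Kenward-Roger degrees of freedom. It needs at least two session groups; with a single group, the group effect cannot be separated from the treatment effect.
- **Reporting.** Give the estimated ICC with its uncertainty. Describe a P<0.05 result as robust to grouping only if the interval from this model agrees.
- **Sample size calculation section.** State that 0.8 assumes no session-group correlation. Add no patients.

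The cost is one extra variable and a few sentences. The downside is that the sensitivity interval will be wider, and with few groups the ICC estimate will be imprecise.
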